# Zopiclone versus placebo for short-term treatment of insomnia in patients with advanced cancer: study protocol for a double-blind, randomized, placebo-controlled, clinical multicenter trial

**DOI:** 10.1186/s13063-018-3088-3

**Published:** 2018-12-27

**Keywords:** Advanced cancer, Insomnia, Pharmacological treatment, Randomized controlled trial

## Abstract

**Background:**

Despite the high prevalence of insomnia in patients with advanced cancer, there are no randomized controlled trials on pharmacological interventions for insomnia in this group of patients. A variety of pharmacological agents is recommended to manage sleep disturbance for insomnia in the general population, but their efficacy and safety in adults with advanced cancer are not established. Thus, there is a need to evaluate the effectiveness of medications for insomnia in order to improve the evidence in patients with advanced cancer. One of the most used sleep medications at present in patients with cancer is zopiclone.

**Methods:**

This is a randomized, double-blind, placebo-controlled, parallel-group, multicenter trial. A total of 100 patients with metastatic cancer who report insomnia will be randomly allocated to zopiclone or placebo. The treatment duration with zopiclone/placebo is 6 consecutive nights. The primary endpoint is patient-reported sleep quality during the final study night (night 6) assessed on a numerical rating scale of 0–10, where 0 = Best sleep and 10 = Worst possible sleep. Secondary endpoints include the mean patient-reported total sleep time and sleep onset latency during the final study night (night 6).

**Discussion:**

Results from this study on treatment of insomnia in advanced cancer will contribute to clinical decision-making and improve the treatment of sleep disturbance in this patient cohort.

**Trial registration:**

ClinicalTrials.gov, NCT02807922. Registered on 21 June 2016.

**Electronic supplementary material:**

The online version of this article (10.1186/s13063-018-3088-3) contains supplementary material, which is available to authorized users.

## Background

Sleep disturbance is frequent in patients with advanced cancer and might impair the tolerance of other symptoms and reduce quality of life [1, 2]. An observational study in different settings of palliative care found that sleep disturbance was reported by 61% of the cancer patients [3]. This prevalence corresponds with results from another multicenter study where 78% of the patients with advanced cancer experienced poor sleep quality [4]. Insomnia is the most prevalent sleep disorder both in the general population and among patients with cancer [5]. The prevalence of insomnia in the general population, when defined according to formal diagnostic systems, is approximately 10% [6, 7]. The prevalence of insomnia in patients with cancer is reported to be threefold higher [8]. Insomnia in the context of cancer is characterized as difficulty initiating sleep and/or difficulty maintaining sleep, which impairs daytime functioning [9].

Sleep quality in patients with advanced cancer might be influenced by several factors such as pain, fatigue, and anxiety, worries about the future, little daytime activity, interrupted sleep because of procedures, a large number of medications, and systemic inflammation [1, 10–12]. In palliative care cancer populations, where life expectancy is limited, the goal of symptom relief usually overrides the concerns of long-term side effects [13]. However, because of polypharmacy and advanced cancer disease, the patients are more vulnerable to potential short-term side effects. Thus, results from studies on pharmacological treatment for insomnia in non-cancer populations are not necessarily applicable to patients with advanced cancer. A careful selection of sleep medications that benefit advanced cancer patients is therefore important.

A combined step-wise pharmacological and non-pharmacological approach is recommended in the treatment of insomnia in cancer patients [14]. In cases where sleep disturbance is due to the cancer or its treatment, the first step is to remove the causative condition if possible (e.g., pain, dyspnea, anxiety) [15]. The second step should include non-pharmacological sleep interventions with cognitive behavioral therapy [16]. Cognitive behavioral therapy for insomnia (CBT-I) usually consists of psychoeducation/sleep hygiene, relaxation training, stimulus control therapy, and cognitive therapy [17]. In a European guideline, CBT-I is recommended as the first line treatment for chronic insomnia in adults of any age [18]. A randomized controlled trial (RCT) supported the efficacy of CBT-I for chronic insomnia associated with cancer [19]. However, a major limitation for the routine implementation of CBT-I in cancer clinics is the lack of mental health professionals formally trained in this approach. In addition, the number of CBT sessions, usually four to eight sessions, can be too demanding for patients during cancer treatment or for patients with advanced cancer disease. Thus, when life expectancy is short, medication is recommended as the treatment of choice for insomnia because of its rapid effect [20, 21].

To manage insomnia successfully, pharmacological treatment for insomnia should reduce sleep latency, increase sleep maintenance, and improve sleep quality [22]. A variety of pharmacological agents against insomnia has been recommended for use in the general population, but their efficacy and safety in adults with cancer are not established [16]. A Cochrane Database review of clinical trials assessing the safety and efficacy of benzodiazepines or benzodiazepine receptor agonists in treating insomnia in palliative care identified no articles that met the inclusion criteria [23]. In 2013, Howell et al. reviewed the evidence base for the management of cancer-related sleep disturbance (insomnia and insomnia syndrome) in oncology practice, and identified no RCT data involving pharmacological interventions for insomnia in advanced cancer [16]. Despite the lack of evidence, several classes of sleep medications are used to treat sleep disturbance in patients with cancer [24]. In a European multicenter study, the most frequently used hypnotic drug was the non-benzodiazepine hypnotic agent zopiclone, which was used by 348 of 2282 patients with advanced cancer [24]. Therefore, we designed a double-blind, placebo-controlled, parallel-group RCT to evaluate the short-term effectiveness of zopiclone on self-reported sleep quality in patients with advanced metastatic cancer who report insomnia.

## Methods

The trial adheres to the Standard Protocol Items: Recommendations for Interventional trials (SPIRIT) checklist (see Additional file 1).

### Study design

This study is designed as a randomized, double-blind, placebo-controlled, parallel-group, multicenter, phase IV clinical trial.

### Study objectives and endpoints

The primary objective is to study the short-time effectiveness of zopiclone on patient-reported subjective sleep quality in patients with advanced cancer who report insomnia. The primary endpoint is patient-reported sleep quality during the final study night with treatment (night 6) assessed on a numerical rating scale (NRS) of 0–10, where 0 = Best sleep and 10 = Worst possible sleep. The secondary objective is to study the effectiveness of zopiclone on mean self-reported total sleep time and sleep onset latency. Table 1 summarizes the objectives and endpoints including the explorative objectives.

**Table 1 Tab1:** Primary, secondary, and explorative objectives and related endpoints and assessments

	Objective	Endpoint	Assessment method
Primary	To study the short-time effectiveness of zopiclone on patient-reported subjective sleep quality	Patient-reported sleep quality the last study night (night 6)	Numerical rating scale 0–10, 0 = Best sleep, 10 = Worst possible sleep
Secondary	To study the short-time effectiveness of zopiclone on patient-reported TST	Patient-reported TST (minutes) the last study night (night 6)	Sleep diary
	To study the short-time effectiveness of zopiclone on patient-reported SOL	Patient-reported SOL (minutes) the last study night (night 6)	Sleep diary
Explorative	To study the short-time effectiveness of zopiclone on overall patient-reported sleep quality	Patient-reported overall sleep quality over a week time interval	Pittsburgh Sleep Quality Index
	To study the short-time effectiveness of zopiclone on objectively measured TST, SOL, SE, WASO, and NWAK	TST (minutes), SOL (minutes), SE (percent), WASO and NWAK during the last study night (night 6)	Actigraphy
	To study the short-time effectiveness of zopiclone on patient-reported TST, SOL, SE, WASO, and NWAK	TST (minutes), SOL (minutes), SE (percent), WASO, and NWAK during the last study night (night 6)	Sleep diary
	To study the short-time effectiveness of zopiclone on self-reported daytime sleepiness	Daytime sleepiness in the morning after night 6	Karolinska Sleepiness Scale

*TST* total sleep time, *SOL* sleep onset latency, *SE* sleep efficiency, *WASO* wake after sleep onset, *NWAK* number of awakenings

### Sample size

The primary variable used in the sample size calculation is patient-reported sleep quality on an NRS of 0–10 during night 6 (the last study night with treatment). The defined minimal clinical important difference (MCID) between the two study groups (zopiclone/placebo) is 2 for the primary outcome sleep quality, scored on the NRS. Due to the lack of relevant data for MCID for NRS on sleep quality, this number was chosen based upon NRS in cancer pain studies [25, 26]. Data obtained in recent studies suggest an expected standard deviation of 2.75 [27–33]. Using a significance level of 5%, these assumptions indicate that for 80% power 33 patients are needed in each group. For 90% power a sample size of 42 per group is required. The study will aim for a 90% power and allow for an expected number of 8 drop-outs during the study period (6 nights). The study will include 50 patients in each treatment arm.

### Eligibility criteria

Patients with advanced cancer with insomnia syndrome will be recruited by study personnel from three outpatient units at hospitals in Norway. Cancer patients are screened using the following two questions: “Do you have problems with your sleep or sleep disturbance on average for 3 or more nights a week?” “Does the problem with your sleep negatively affect your daytime functioning?” Informed consent will be obtained for all patients included in the study.

#### Inclusion criteria

The criteria for inclusion in the study are:Histologically verified malignant diseasePresence of metastatic/disseminated diseasePresence of insomnia syndrome in the context of cancer defined as [9]:◦ Self-reported difficulty initiating sleep (greater than 30 min to sleep onset) and/or difficulty maintaining sleep (greater than 30 min nocturnal waking time) and/or waking up earlier than desired; and◦ Sleep difficulty at least 3 nights per week; and◦ Sleep difficulty that causes significant impairment of daytime functioning (the patient will be asked if sleep difficulty results in altered daytime function, i.e., feeling tired, lack of energy)Patient at least 18 years of ageAbility to comply with all study proceduresProvision of signed informed consent

#### Exclusion criteria

The following criteria are grounds for exclusion from the study:Ongoing treatment or previous treatment (within last 4 weeks) for more than 3 consecutive days with medications given for insomniaAdverse reactions to zopicloneHistory of substance abuseConcomitant use of rifampicin and erythromycinAny other contraindication listed on the summary of product characteristics of zopiclone◦ Myasthenia gravis◦ An established diagnosis of severe impairment of respiratory function◦ An established diagnosis of severe hepatic insufficiency (Child-Pugh grade B or C)◦ An established diagnosis of sleep apnea◦ Known hypersensitivity to the drug or to any component in its formulationUnfit for participation for any reason as judged by the investigatorPregnancy or lactationWomen of reproductive age not willing or unable to employ an effective method of contraception (sterilization, using IUD or oral contraception)Scheduled surgery within the next weekNeeding change in scheduled opioid dose at baseline (study visit 1)Scheduled intravenous administration of chemotherapy during the study period (from baseline to day 8) or intravenous administration of chemotherapy during the last weekChange in corticosteroid dose last week before baseline or planned dose change in corticosteroid dose within 7 days from baseline

### Randomization, blinding, and study monitoring

Patients who have consented to participate in the study will be randomized using a web-based randomization system developed and administered by the Unit for Applied Clinical Research, Institute of Cancer Research and Molecular Medicine, Norwegian University of Science and Technology (NTNU), Trondheim, Norway. Patients are randomized to either the zopiclone arm (Arm A) or the placebo arm (Arm B) (Fig. 1). Randomization will be stratified based on study center. Patients are allocated with equal probabilities to treatment. The treatment is double-blind; i.e., the investigational medicinal product (IMP) is blinded for the patient, site, and study personnel by identical appearance, shape, and color as well as identical labeling and packing. In a medical emergency, the investigator will be able to break the code for an individual patient by contacting the person on call at the hospital pharmacy. The external monitor for the trial is the Unit for Applied Clinical Research, NTNU.

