### Data collection and statistics

The following variables will be recorded in the web-based case report form, which is administered by the Unit for Applied Clinical Research, (NTNU): date of birth, weight, height, concomitant diseases, psychiatric history, department category (i.e., palliative care unit or general oncology ward), principal cancer diagnosis (International Classification of Diseases (ICD-10)), date of the principal cancer diagnosis, site of metastases (bone, liver, lung, central nervous system, other), present anticancer treatment, and medications taken in the last 24 h. The Karnofsky Performance Status (KPS) scale will be used to assess performance status [34]. In addition, history and duration of opioid consumption will be obtained. Clinical chemistry results (hemoglobin, creatinine, C-reactive protein, albumin, and bilirubin) will be obtained from the medical record. Results collected less than 7 days before inclusion are considered valid.

The following populations will be considered for the analyses: (1) intention-to-treat population: all randomized patients regardless of protocol adherence; (2) per-protocol population: includes all subjects who have completed the study medication. A safety analysis will be performed, which includes all subjects who have received at least one dose of study medication. Subjects who withdraw from the study will be included in the safety analysis. The main statistical analysis will be performed when the target number of 100 patients has been recruited. Baseline characteristics will be summarized by mean and standard deviations (SDs) for continuous variables, and counts and percentages for categorical variables. The 11-point NRS for sleep quality is regarded as continuous. Comparison of means will be performed with the Student’s *t* test for continuous variables. The study follows the Consolidated Standards of Reporting Trials (CONSORT) recommendations for reporting RCTs. A *p* value of ≤0.05 will be considered statistically significant when comparing the two groups for the primary endpoint or the two secondary endpoints. Statistical analyses will be performed with SPSS version 25, IBM Statistics, Chicago, IL, USA.

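### Randomization is stratified by center but the named t test has no center term: an avoidable efficiency loss if centers differ, not a threat to validity

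*Protocol article*

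**What the plan says.** Under Randomization, blinding, and study monitoring the article states "Randomization will be stratified based on study center" and "Patients are allocated with equal probabilities to treatment". No other stratification factor is named, and no block scheme is described. Under Eligibility criteria, recruitment is from "three outpatient units at hospitals in Norway", which I take to be the three strata.

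Under Data collection and statistics the analysis is fixed as "Comparison of means will be performed with the Student’s *t* test for continuous variables", after "The 11-point NRS for sleep quality is regarded as continuous". The same paragraph sets the 0.05 criterion for the primary and the two secondary endpoints. It mentions no center term, stratified test or covariate model. The Sample size section is likewise built on a plain two-group comparison: "The defined minimal clinical important difference (MCID) between the two study groups (zopiclone/placebo) is 2 for the primary outcome sleep quality" and "Data obtained in recent studies suggest an expected standard deviation of 2.75".

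**The concern.** Randomizing separately within each center normally keeps the arms balanced there. Differences in mean sleep score between centers then largely cancel out of the treatment difference. A two-sample t test does not know this: it pools all patients within an arm and counts the between-center spread as random error. If that spread is real, the reported standard error exceeds the true sampling error, confidence intervals are wider than they need be, and the test rejects less often than 5% under the null. Precision that stratification could have delivered goes unused on all three endpoints held to the 0.05 criterion.

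**Working it through.** **Inputs.** From the Sample size section: difference 2 NRS points, SD 2.75, 42 per group for 90% power, 5% level. Sidedness is not stated; two-sided is assumed. From the sections cited above: three centers, equal allocation, t test. Assumed, because not in the article: the share ρ of total outcome variance lying between centers (0 to 15%), and balance of the arms within center.

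**1. The plan's own figure.** A two-sided 5% two-sample t test with difference 2 and SD 2.75 needs 30.7, so 31, per group for 80% power and 40.7, so 41, for 90%. The article gives 33 and 42, within two patients. At 42 per group the t-test power is 90.9%. In the normal approximation, SE = 2.75 × √(2/42) = 0.600, 2/0.600 = 3.333, and power = Φ(3.333 − 1.960) = 91.5%.

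**2. Effect of ignoring center.** Split the variance 2.75² = 7.5625 into ρ × 7.5625 between centers and (1 − ρ) × 7.5625 within. With balance inside each center, the true standard error of the difference is √(1 − ρ) times the one the t test uses. Hence:

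- overstatement of the standard error = 1/√(1 − ρ) − 1
- true level = 2 × [1 − Φ(1.960/√(1 − ρ))]
- power without center = Φ[(2/SE − 1.960)/√(1 − ρ)]
- power with center = Φ[2/(SE × √(1 − ρ)) − 1.960]

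Example, ρ = 0.10: √0.90 = 0.949. Level = 2 × [1 − Φ(2.066)] = 3.9%. Power without center = Φ(1.373/0.949) = 92.6%; with center = Φ(3.333/0.949 − 1.960) = 94.0%.

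| ρ | SE overstated | true level | power, no center | power, center |
|---|---|---|---|---|
| 0 | 0% | 5.0% | 91.5% | 91.5% |
| 0.02 | 1.0% | 4.8% | 91.7% | 92.0% |
| 0.05 | 2.6% | 4.4% | 92.1% | 92.8% |
| 0.10 | 5.4% | 3.9% | 92.6% | 94.0% |
| 0.15 | 8.5% | 3.4% | 93.2% | 95.1% |

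Power rises with ρ in both columns because the total SD is held at 2.75; the loss is the gap between the columns.

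**3. Simulation.** With 42 per arm and exact balance within center, the t test's level was 4.4%, 3.9% and 3.5% at ρ = 0.05, 0.10 and 0.15. Power without and with center was 91.5% and 92.2%, 92.2% and 93.7%, and 92.5% and 94.7%. The losses are 0.7, 1.5 and 2.2 points, close to the formula, which ignores estimation of the variance.

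A second simulation used unequal centers (about 50%, 30% and 20% of patients) and permuted blocks of 4, with 10,000 runs per setting. At ρ = 0.10 it gave a level of 4.0% for the t test and 5.3% with center. The Monte Carlo standard error near 5% is about 0.2 points.

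**4. Control.** With unstratified allocation and ρ = 0.10 the t test held its level (5.1%). The shortfall in level therefore comes from balancing on center and then leaving center out.

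**5. What ρ means on the scale.** For three equal centers with evenly spaced means, the gap between extreme centers is 2 × √(1.5 × ρ × 7.5625). If two centers coincide and one differs, it is 3 × √(ρ × 7.5625/2). This gives 0.8 to 1.0 points at ρ = 0.02, 1.3 to 1.5 at 0.05, 1.8 to 2.1 at 0.10, and 2.3 to 2.6 at 0.15.

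**The case against.** The strongest reply is that this is an efficiency preference and that its size is unknown. Most of that stands.

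- The shortfall needs centers that really differ. The 10% and 15% cases require gaps between centers of about 2 NRS points or more, the size of the treatment difference the trial is built to detect. Nothing in the article points to gaps that large among three outpatient units sharing one set of eligibility criteria. At 2% the loss is 0.3 points of power.
- It also needs balance within center. Balance is the usual purpose of stratifying, but the article does not describe blocking or any equivalent.
- In every case examined the unadjusted test exceeds the planned 90% power at 42 per arm, and the sample size was itself derived from a two-group comparison without center.
- A fuller analysis plan may already include center. That lowers the priority, but the article names the t test without deferring the choice elsewhere.

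A reader might infer that the trial's conclusions would be unsafe, that false positives become more likely, or that the trial is underpowered. The documents support none of these. The error, where there is one, is conservative, so a significant result would stand. Nor can one say without condition that the test runs below 5%: with equal center means it runs at 5%.

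**Conclusion.** The mismatch between the stratified randomization and the named analysis is in the text, and its direction is clear. Its size is conditional and modest: a true level of about 4.8% to 3.5%, and about 0.3 to 2.2 points of power forgone, for between-center shares of 2% to 15%. The lower end looks the more plausible on what the article shows.

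The figures assume balance within center, a two-sided 5% test, a total SD of 2.75 and 42 analysed per arm. The level figures carry over approximately to the two secondary endpoints at the same variance share. The power figures apply only to the primary endpoint, because the article gives no SD or target difference for the others. The point is a low-cost improvement in efficiency and interval accuracy, not a defect in validity.

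**What to change.** In Data collection and statistics, replace the t test for the primary endpoint and both secondary endpoints with a linear model containing treatment and study center as a three-level fixed factor. Report the treatment difference and its confidence interval from that model.

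The cost is one phrase and two degrees of freedom (80 instead of 82 residual with 84 patients analysed). If centers do not differ, simulated power is the same to the first decimal (91.3% with and without center). Recruitment was still open when the article was published and the main analysis follows the 100th patient, so as of that document the change could be specified before unblinding. Whether to adjust for other variables, such as the baseline score, is a separate question that this point does not address.

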**Fig. 1 Fig1:**
[figure not shown]
Consolidated Standards of Reporting Trials (CONSORT) flow diagram

### Treatment

The treatment is 6 subsequent nights with zopiclone or placebo. For this study, zopiclone “Actavis” 3.75 mg, 5 mg, and 7.5 mg (active comparator) are defined as the IMP. Kragerø Tablettproduksjon AS, Kragerø, Norway will produce, blind, pack, and label the IMP. Patients will receive the IMP in custom-made capsules containing zopiclone Actavis 3.75 mg, 5 mg, or 7.5 mg or placebo administered once daily (taken in the evening 30 min before going to bed). Each patient will receive six boxes, with each box containing the allocated IMP for 2 nights. Each box is labeled with dose level according to the titration. The initial dose of zopiclone/placebo is 3.75 mg/day started after 1 night with sleep quality assessment and symptom assessment. The study personnel will evaluate the patient by phone after 2 and 4 nights of being on study medication by asking the question “Please circle the number that best describes how you feel now” on an NRS, where 0 = Best sleep and 10 = Worst possible sleep. If the NRS value is ≥4 at evaluation (Fig. 2), the dose of zopiclone/placebo is increased one dose level according to dose level 1 = 3.75 mg zopiclone/placebo; dose level 2 = 5 mg zopiclone/placebo; dose level 3 = 7.5 mg zopiclone/placebo. If NRS is < 4 at evaluation, the patient continues on the same dose level. If patients titrated to dose level 2 at night 4 experience excess sedation during the daytime, the dose can be decreased to dose level 1 for nights 5 and 6. The patients will indicate in the sleep diary whether they have taken their trial drug or not and state the reason, given by the alternatives forgotten, side effects, or other, if they omitted the trial medication. Each patient will be instructed to contact the investigator immediately should they manifest any signs or symptoms they perceive as serious. End-of-protocol therapy is defined as therapy after 6 nights with treatment. Further treatment is the responsibility of the physician in charge of patient treatment. The protocol was considered as a low-risk study, and according to Norwegian legislations, a data monitoring committee was not needed.

